## Abstract

**Background:**

Autism Spectrum Disorder (ASD) is a neurodevelopmental disorder characterized by deficits in social interaction, repetitive behavior and language impairment, and its worldwide prevalence has been found to be increasing annually in recent years. Till now, ASD is uncurable as its pathogenesis remains unknown. However, studies on both animals and humans have demonstrated that fecal microbiota transplantation (FMT) may ameliorate the symptoms of ASD, as well as gastrointestinal symptoms. Nonetheless, there is still no agreement regarding the optimal dosage or duration of FMT treatment for individuals with ASD.

**Methods:**

This clinical study is a double-blind, randomized, interventional trial conducted at a single center. The aim is to investigate the safety and efficacy of a pediatric formulation of FMT for ASD. A total of 42 children between the ages of 3–9 with ASD will be randomly assigned in a 2:1 ratio to either an FMT treatment group (*n* = 28) or a placebo group (*n* = 14), forming cohort 1. Additionally, 30 healthy children of similar age and gender will be recruited as the control group (cohort 2). Cohort 1 will be assessed using a variety of scales, including the Autism Behavior Checklist, Childhood Autism Rating Scale, Social Responsiveness Scale, Gastrointestinal Symptom Rating Scale, Children’s Sleep Habits Questionnaire, and Psychoeducational Profile (Third Edition). These assessments will evaluate the effectiveness of FMT in reducing core symptoms and comorbidities (such as gastrointestinal symptoms and sleep disturbances) in children with ASD. The study will use metagenomic and metabolomic sequencing to assess changes in the composition and structure of the intestinal flora and its metabolites in blood, urine, and feces following treatment. Furthermore, the study will evaluate the acceptability of the FMT formulation by participants’ legal guardians and investigate differences in the intestinal flora and metabolism in the FMT group before and after treatment compared to 30 healthy children.

**Clinical trial registration:**

https://www.chictr.org.cn/, identifier ChiCTR2200058459.

## Introduction

1.

Autism Spectrum Disorder (ASD)^1^ is a complex neurodevelopmental disorder characterized by core features such as social deficits, stereotyped behaviors, and language impairments (Coretti et al., 2018). Over the past 20 years, there has been a significant rise in the prevalence of ASD, with the current rate in the US estimated to be 1 in 44 children according to the 2021 CDC report, posing a significant challenge to both public health and families. In addition to genetic factors, gut microbes and their metabolites have become a popular area of research in recent years (Qi et al., 2021). The human gut contains approximately 40 trillion bacteria, which is 5–10 times more than the total number of cells in the body. This microbial population also has approximately 150 times more genes than the human body, often called the “second brain” of the body (Sun et al., 2019). It is reported that people with ASD often suffer from a combination of gastrointestinal symptoms such as constipation and diarrhea, as well as altered gut microbiology, mainly in the form of abnormal bacteria and metabolites (Rose et al., 2018). For individuals with ASD, gastrointestinal symptoms aggravate their sleep problems, and conversely inadequate sleep quality and quantity also aggravate their ASD symptoms (Cortese et al., 2020). In addition, children with ASD who suffer from sleep disorders also suffer from imbalances in their gut flora (Han et al., 2022).

The gut microbiota is highly specific, which can lead to varying conclusions among different studies regarding the gut microbiota characteristics in individuals with ASD. Research has shown that compared to healthy individuals, children with ASD tend to have a deficiency of beneficial gut bacteria. Further, there is higher level of Bacteroidetes, Firmicutes, and Actinobacteria at the phylum level in children with ASD. At the genus level, children with ASD tend to have higher level of Prevotella, Faecali bacterium and Bacteroides while having lower levels of Akkermansia and *Bifidobacterium longum* (Ristori et al., 2019; Iglesias-Vazquez et al., 2020; Zou et al., 2020). Patients with both severe ASD and high Bacteroidetes have significantly higher total short-chain fatty acids (Qi et al., 2021), and in pregnant rats, it was found that abnormalities in these total short-chain fatty acids could lead to ASD-like behavior in their offspring (Alharthi et al., 2022). Patients with ASD exhibit abnormal levels of plasma tryptophan and glutamate and their respective metabolites. Also, both tryptophan and glutamate, along with their metabolites, have significant impacts on brain development (Montanari et al., 2022). Microorganisms in the gastrointestinal tract play a crucial role in regulating amino acid digestion, absorption, synthesis and metabolism and also have an impact on the central nervous system of the host (Lin et al., 2017). Tryptophan plays an important role in the pathogenesis of ASD (Wang et al., 2020). Changes in gut microbiota can impact tryptophan metabolism, and the administration of probiotics can facilitate the conversion of tryptophan to serotonin, also known as 5-hydroxytryptamine (Kong et al., 2022). Short-chain fatty acids found in the gut can down-regulate the expression of the Neurexins gene and increase the production of catecholamines, ultimately leading to improved ASD symptoms in rats (Nankova et al., 2014). Gut microbes produce signaling molecules that promote the synthesis of neurotransmitters such as serotonin, dopamine, and gamma-aminobutyric acid. Furthermore, studies have shown that *Bifidobacterium longum* can improve neuroinflammation resulting from tryptophan abnormalities in rats with Autism Spectrum Disorder (ASD) (Liu et al., 2021). The bidirectional communication between gut microbes and the central nervous system forms a “microbe-gut-brain axis (Bonaz et al., 2018), which may regulate neurodevelopment and neurodegenerative diseases, including Autism Spectrum Disorder, anxiety and depression, Alzheimer’s disease, and Parkinson’s disease, through metabolic, vagal, and immune modalities (Fattorusso et al., 2019; Ansari et al., 2020). Although the mechanism linking gut microbes to the pathogenesis of ASD remains unknown, studies have shown that mice transplanted with gut flora from children with autism develop autistic symptoms (Sharon et al., 2019). Therefore, bacterial and metabolic markers may play a significant role in the pathogenesis of ASD, but further research is necessary to identify these markers.

Fecal microbiota transplantation (FMT) is a procedure that involves transferring fecal microorganisms from a healthy individual to a patient’s gastrointestinal tract, with the aim of improving the intestinal microecology and treating the disease (Liu et al., 2022). Studies have shown that FMT can improve symptoms of ASD, as well as gastrointestinal symptoms and intestinal microecology (Tan et al., 2021). The intestinal microecology is diverse and complex, and FMT contains around 1,000–1,150 functional bacteria that colonize the host gut more efficiently than prebiotics or probiotics (Vendrik et al., 2020). Although no serious adverse events have been identified in studies of FMT for ASD, clinical adverse effects such as fever and allergies have been observed in children with ASD treated with FMT (Zhao et al., 2019). Therefore, the efficacy and safety of FMT need to be further evaluated. More research is needed to understand how FMT improves ASD symptoms by altering intestinal flora and metabolites (Xu et al., 2021). Additionally, there is still no consensus on the optimal dose or duration of FMT for the treatment of ASD. This study is a double-blind randomized controlled trial with the primary aim of assessing the improvement of ASD symptoms with FMT. By analyzing the correlation between changes in the scale of autism-related symptoms and gut flora and metabolites in a reasonable grouping, sample size, dosing method and treatment phase, we sought to identify the unique bacterial and metabolic markers of ASD that may provide additional evidence for the “microbial-gut-brain axis” and the treatment of ASD symptoms with FMT. This study will have important implications for treating patients with ASD associated with gut microecological dysbiosis.

This is a double-blind randomized controlled trial aimed at assessing the effectiveness of FMT in improving symptoms of ASD (Figure 1). The main objective of this study is to evaluate the effectiveness of the FMT technique in improving symptoms in children with ASD and to identify the core symptoms of ASD that can be improved by FMT. Additionally, there are four secondary aims: (1) to compare changes in the composition of gut flora in children with ASD before and after FMT, (2) to compare differences in gut flora between children with ASD and healthy children, (3) to assess the safety of the FMT pediatric formulation in children with ASD, and (4) to evaluate the acceptability of the FMT pediatric formulation to children with ASD and their legal guardians. The exploratory aim of the study is to identify changes in the metabolomics of children with ASD before and after receiving FMT.

**Figure 1 fig1:**
[figure not shown]
An experimental FMT treatment group (*n* = 28) and a placebo group (*n* = 14) are set up, with healthy children (*N* = 30) as controls. A series of scales and metagenomic and metabolomic sequencing of blood, urine, and feces will be used to compare the results of the three groups.

## Methods and analysis

2.

### Study design

2.1.

This is a single-center, double-blind, double-modeled, randomized, interventional clinical study aiming at exploring the efficacy and safety of FMT formulation on an interventional treatment of children with ASD. The degree of improvement in their symptoms will be assessed using several scales. Additionally, changes in the composition and structure of their intestinal flora and metabolites of the flora in their blood, urine and feces before and after treatment will also be assessed by macro-genomic sequencing and metabolomics. The study will also evaluate the differences in the gut flora of children with ASD and healthy children and the acceptability of FMT pediatric preparations by children with ASD and their legal guardians.

The primary endpoint of the study is the change from baseline in Childhood Autism Rating Scale (CARS) scores in children with ASD after 12 and 24 weeks of treatment. The secondary endpoints are the variations in assessment scales, and gut flora and included five main points:

(1) Variations in scores from baseline in the Social Responsiveness Scale (SRS), Autism Behavior Checklist (ABC), Psychoeducational Profile Third Edition (PEP3), Gastrointestinal Symptom Rating Scale (GSRS), and Children’s Sleep Habits Questionnaire (CSHQ) after 12 and 24 weeks of treatment;(2) Variations in gut flora characteristics (including alpha-diversity, flora composition, beta-diversity, colonizing bacteria, differential bacteria, and metabolic pathway function) in children with ASD after treatment compared to baseline and donors;(3) Differences in intestinal flora characteristics (including alpha-diversity, flora composition, beta-diversity, differential bacteria, and metabolic pathway function) between children with ASD (baseline) and healthy children;(4) The incidence of adverse events during the treatment of children with ASD;(5) Variations in the FMT acceptance scale scores for participants with ASD and their legal guardians.

The patients will be divided into two cohorts: Cohort 1 will include 42 children aged 3–9 years diagnosed with ASD, while Cohort 2 will include 30 healthy children aged 3–9 years. The sex ratio and age range of children enrolled in Cohort 1 and Cohort 2 will be kept roughly the same. In Cohort 1, subjects who meet the entry criteria will undergo a two-week screening visit after the legal guardian signs the informed consent. They will then be randomly allocated to either the trial or control group in a 2:1 ratio. Children in the trial group will undergo rehabilitation and FMT, while the control group will receive rehabilitation and placebo. All children will undergo a 12-week treatment period following the completion of bowel preparation and followed up for 12 weeks, during which they will receive only rehabilitation. A homogenous rehabilitation scheme will be performed on all the ASD children in Cohort 1. The study participants will be discharged at week 25 after the end visit. In Cohort 2, after the legal guardian signs the informed consent, they will undergo a physical examination, assessment of vital signs, and various laboratory examinations within two weeks to confirm their health status. Blood, urine, and fecal samples will be collected within one week, and the children will be discharged. Metabolomics analysis will be performed on blood and urine samples, while macro-genomic sequencing and metabolomics analysis will be conducted on fecal samples.

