### Sample size estimation

2.3.

For Cohort 1, a total of 42 subjects will be randomized in a 2:1 ratio (28 in the trial arm: 14 in the control arm) to provide sufficient statistical power for determining the effectiveness of FMT in improving CARS scores compared to placebo. It is anticipated that, after 25 weeks of treatment, the mean reduction in CARS scores for the FMT group will be 5 points. Additionally, using a one-sided alpha level of 5 and 80% power, the proposed sample size will be able to detect the expected differences between the two groups. Considering a 15% dropout rate, the final sample size for Cohort 1 is expected to be 42 cases.

For Cohort 2, a sample size of 30 cases is considered sufficient to compare gut flora differences between children with ASD and healthy children.

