**Figure 2 fig2:**
[figure not shown]
Overall process of the clinical trial.

**Table 1 tab1:** Inspection schedule for cohort 1.

Parameters	Baseline	Bowel preparation	Treatment period						Follow-up
			First dose treatment	Intensive treatment	Maintenance treatment				
Time window	D-21 ~ D-7	D-6 ~ D-1	D1 ~ D7	D8 ~ D28	D29 ~ D42	D43 ~ D56	D57 ~ D71	D71 ~ D84	D85 ~ D169
Informed consent	X								
Inclusion and exclusion criteria	X								
Demographic data^a^	X								
Medical and treatment history	X								
Height	X								
Weight	X							X	X
Vital signs^b^	X							X	X
Allergy history	X								
Health checkup	X							X	X
Routine blood test	X							X	X
Blood biochemistry	X							X	X
Urinalysis	X							X	X
Fecal routine	X							X	X
Fecal sample collection^c^	X			X		X		X	X
Urine sample collection^c^	X			X		X		X	X
Blood sample collection^c^	X							X	X
Bowel preparation		X							
FMT			X						
CARS	X			X		X		X	X
SRS	X			X		X		X	X
GSRS	X			X		X		X	X
ABC	X			X		X		X	X
CSHQ	X			X		X		X	X
PEP3	X			X		X		X	X
rehabilitation training	X								
Acceptance survey^d^			X	X				X	
Diet Record	X								
Adverse event record	X								
Combined medication record	X								

FMT, Fecal Microbiota Transplantation; CARS, Childhood Autism Rating Scale; GSRS, Gastrointestinal Symptom Rating Scale; ABC, Autism Behavior Checklist; PEP3, Psychoeducational Profile(Third Edition); SRS, Social Responsiveness Scale; CSHQ, Children’s Sleep Habits Questionnaire.

1 Demographics: date of birth, age, sex, ethnicity.

2 Vital signs: temperature, blood pressure, heart rate (pulse), respiratory rate.

3 Sample collection:

a Stool sample collection: Stool samples will be collected for macro-genome sequencing and metabolomic analysis during the screening period, every fortnight after the start of treatment for macro-genome sequencing, and every four weeks for metabolomic analysis until the end of the study.

b Urine sample collection: Urine samples will be collected for metabolomic analysis during the screening period and every four weeks from the start of treatment until the end of the study.

c Blood sample collection: Blood samples will be collected for metabolomic analysis during the screening period, at the end of treatment (week 13), and at the end of the study (week 25) for metabolomic analysis and safety data collection in the blood.

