### Statistical analysis

2.6.

Bioinformatics and statistical analyses will be conducted by professionals using specialized software tools. Analysis of clinical scale results will involve comparing changes in ABC, CARS, SRS, GSRS, CSHQ and PEP3 scales before and after FMT. Differences in scale results between pre- and post-treatment and control groups will also be assessed. To analyze gut flora and metabolites, we will examine alpha-diversity, beta-diversity, bacterial symbiotic networks, and metabolome analysis using the R language MetaboAnalystR package. This package will enable the quantification of metabolite content and the identification of characteristic metabolites. Mann–Whitney U and Kruskal-Wallis tests will be used to analyze differences in gut flora and metabolites between groups. To explore the correlation between gut flora, metabolites, and improvements in ASD symptoms, gastrointestinal symptoms, and sleep symptoms, we will use Spearman’s correlation test.

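### Secondary endpoint (2) judges gut flora, including colonizing bacteria, against baseline and donors without naming placebo; that comparison alone cannot separate donor transfer from background gain

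*Protocol article*

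**What the plan says.** Section 2.1 (Study design) lists the flora characteristics under secondary endpoint (2) as "alpha-diversity, flora composition, beta-diversity, colonizing bacteria, differential bacteria, and metabolic pathway function", assessed "in children with ASD after treatment compared to baseline and donors". Endpoint (3) in the same list names a different comparator, healthy children, and leaves colonizing bacteria out.

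Other places bear on which groups are compared:

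- Introduction, secondary aim (1): "to compare changes in the composition of gut flora in children with ASD before and after FMT".
- Abstract, Methods: flora and metabolism in the FMT group, before and after treatment, set against the 30 healthy children.
- Section 2.1, on allocation: the trial group receives rehabilitation and FMT, "while the control group will receive rehabilitation and placebo".
- Figure 1 legend: the scales and sequencing "will be used to compare the results of the three groups", that is, FMT, placebo and healthy children.
- Section 2.6: Mann–Whitney U and Kruskal-Wallis "tests will be used to analyze differences in gut flora and metabolites between groups". The groups are not named, and neither donors nor colonization is mentioned.
- Table 1 footnote on stool sampling: samples are taken at screening and then "every fortnight after the start of treatment for macro-genome sequencing". The schedule is for Cohort 1 as a whole.

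**The concern.** The trial has a randomised placebo arm, but the endpoint that would show whether donor bacteria establish themselves is worded around two other comparators. A child's flora can come to include taxa that a donor also carries without any transfer, through normal turnover, through taxa crossing the detection limit, or through regrowth after bowel preparation. Section 2.5.2.1 applies bowel preparation, ending in polyethylene glycol cleansing, to both arms, so some shift is plausible in placebo children too. Comparison with baseline and donors does not remove any of this. Comparison with placebo children scored in the same way does.

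What is at stake is the mechanistic reading of the trial. The Introduction aims to identify bacterial markers, section 2.6 plans to correlate flora with symptom improvement, and the Discussion rests the high first-week dose on colonization after antibiotics. A colonization figure that includes an unknown background would be weak support for that chain.

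**Working it through.** **Arm sizes.** Section 2.3 gives 42 children randomised 2:1. 42 × 2/3 = 28 FMT and 42 × 1/3 = 14 placebo, as stated.

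**What the texts fix.** Endpoint (2), aim (1) and the abstract are all worded as before/after, with donors or healthy children as the reference. The Figure 1 legend and section 2.6 point to comparison between groups, but neither says that FMT versus placebo is the contrast for colonization or donor similarity. The documents therefore leave the randomised contrast open for this endpoint and do not state it.

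**Why the contrast matters.** The documents give no rate of chance gain and no transfer rate, and do not define colonization. The following is an assumption for illustration only. Count a child as colonized if a donor feature is absent at baseline and present later. Let c be the probability of such a gain without transfer, and t the probability of transfer among the rest.

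- Apparent rate in the FMT arm: f = c + (1 − c)t
- Placebo rate under the same rule and the same donor reference: c
- FMT minus placebo: f − c = (1 − c)t

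With t = 0, the FMT arm shows 28c children as colonized and the placebo arm 14c:

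| c | FMT, of 28 | Placebo, of 14 | Difference in rates |
|---|---|---|---|
| 0 | 0 | 0 | 0 |
| 0.05 | 1.4 | 0.7 | 0 |
| 0.10 | 2.8 | 1.4 | 0 |
| 0.20 | 5.6 | 2.8 | 0 |
| 0.30 | 8.4 | 4.2 | 0 |

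With t = 0.30:

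| c | FMT apparent rate | Placebo rate | FMT minus placebo |
|---|---|---|---|
| 0 | 30% | 0% | 30 points |
| 0.05 | 33.5% | 5% | 28.5 points |
| 0.10 | 37% | 10% | 27 points |
| 0.20 | 44% | 20% | 24 points |
| 0.30 | 51% | 30% | 21 points |

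The FMT-arm figure rises with c although transfer is unchanged. With no transfer, the difference is zero at every c. With transfer, it is (1 − c)t, so dividing by (1 − c), one minus the placebo rate, recovers t. At c = 0 there is no bias.

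**Precision.** Fourteen placebo children estimate the background only roughly. The exact 95% interval is 0 to 23% if none gains a donor feature, and 5% to 51% if three do. The contrast therefore needs to be reported with its interval.

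**The case against.** The strongest reply is that the article does not name placebo in its endpoint wording generally. The primary endpoint is simply change from baseline in CARS, yet section 2.3 makes clear that CARS is compared with placebo. On that view, endpoint (2) defines the variable, while the Figure 1 legend and section 2.6 supply the contrast; both tests named in section 2.6 are for independent groups. This has force, and a placebo comparison of flora may well be intended. What remains is that no sentence does for colonization what section 2.3 does for CARS, and that aim (1) and the abstract point towards before/after FMT.

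A reader might go further and infer three things that the documents do not support.

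- That the 14 placebo children cannot be scored because they have no donor. Endpoint (2) refers to donors in general, the Discussion describes standard bacterial fluids, and no pairing of child with donor is described. Placebo children can be scored against the same donor profiles.
- That colonization will be reported in the FMT arm only. The endpoint covers children with ASD, and no text restricts it to one arm.
- That the plan counts any gain of a donor taxon as transfer. Colonizing bacteria are not defined, and a stricter rule is equally compatible with the text. The scoring algorithm is also detail that a condensed article may leave to the full protocol, so its absence alone is no fault.

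**Conclusion.** The point holds in a limited form. As worded, endpoint (2) compares flora, including colonizing bacteria, with baseline and donors and leaves the randomised placebo contrast unstated. The general between-group statements elsewhere do not settle it. A before/after-versus-donor figure by itself cannot separate transfer from background gain. The size of that background cannot be derived from the documents; the figures above rest on assumed rates and vanish at c = 0.

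Severity is minor. Colonizing bacteria are one of six flora characteristics within one secondary endpoint, and the primary CARS analysis and the sample size do not depend on them. One limit applies to the remedy: the placebo contrast removes only what both arms share. Section 2.5.2.1 speaks of rifaximin suspension or a mimetic without making clear whether both arms receive the active drug. If they do not, an antibiotic effect would stay in the difference.

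**What to change.** State in secondary endpoint (2) that:

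1. children in both arms are scored by one rule against the same donor (product-batch) reference;
2. the FMT-minus-placebo difference, with its confidence interval, is the measure of colonization and of similarity to donor, and the before/after figures are descriptive;
3. scoring is done after database lock, because a child's similarity to the donors could reveal allocation while section 2.4 still requires the blind.

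Align the abstract, secondary aim (1), the Figure 1 legend and section 2.6 with this wording, and name in section 2.6 the groups that the flora tests compare.

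The cost is wording and some additional bioinformatics. No new samples are needed: the stool schedule in Table 1 already covers all of Cohort 1, and the endpoint already requires donor profiles. If chance gains occur, the reported colonization figure will be lower than the uncorrected one, and its interval will be wide with 14 placebo children.
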